### Step 6: Evaluation of the Program

A clustered quasi-experimental trial with three conditions will be used to evaluate the intervention (see Figure 4). We use a quasi-experimental design in which participants can be part of three different groups. First, a researcher recruits patients and randomly allocates them into an intervention (Group 1) or control group (Group 2). Next, a GP recruits patients into the other intervention group (Group 3). In both intervention groups, participants will not be randomly allocated to one of the behavior groups of the intervention (ie, PA, fruit, or vegetables), but participants can choose themselves for which behavior they want to complete the intervention. Group 1 is an intervention group in which researchers select and motivate adults to use the intervention by offering a flyer and/or tablet. In Group 3, the selection and motivation of adults will be randomly conducted by GPs in the waiting room by offering a flyer and/or tablet. Participants of both groups will receive a flyer with a personal code and can choose to start the intervention program in general practice on a tablet or at home on the website. Group 2 will be a waiting-list control group in which adults are randomly selected by a researcher. Participants in this control group only have to fill in a questionnaire and have no access to the computer-tailored feedback, action planning part, or to the evaluation in the follow-up modules. After completing the questionnaire at baseline and at the 1-month follow-up, the control group will also get access to the intervention modules.

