In total, 30 adults will be selected in each of 15 general practices (n=450). First, a researcher will select 10 patients that will be allocated to the intervention group and 10 patients that will be allocated to the control group. Next, GPs will be asked to recruit another 10 patients to complete the intervention program. In this way, it can be evaluated whether GPs' involvement leads to more sustained use of the eHealth intervention, and higher levels of PA and FV intake. In both intervention groups, adults will be invited to complete session 1 either on a tablet in general practice or on their computer at home. Adults who do not use the tablet have to fill out a short questionnaire and leave their email address to be sent a reminder email to complete session 1 at home. After 1 week and 1 month of completing session 1, adults will receive an email to respectively start sessions 2 and 3. In the control group, adults will have to fill out a questionnaire at baseline in general practice or at home and at 1-month postintervention. To prompt adults to complete all questionnaires and sessions, reminder mails and SMS text messages will be sent. Inclusion criteria for participating in the study in both intervention and control groups are as follows: at least 18 years old, understand Dutch language, have an email address, and have access to the Internet. The outcome measures—increase in PA level, increase in FV intake, and self-regulation skills from baseline to postintervention—will be compared for the control and intervention conditions by conducting repeated measures multivariate analyses of variance (MANOVAs). Participant characteristics (ie, socioeconomic status [SES], age, sex, health status, and reaching health norms) will be compared at baseline. Characteristics that differ for the intervention and control groups will be added as covariates in further analyses. Furthermore, multilevel analyses will be conducted to take into account the clustering of participants into general practices.

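### Covariates are to be chosen because they differ between groups at baseline; a fixed set of the five named characteristics would serve both the randomised and the GP-recruited comparison better

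*Protocol article*

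**What the plan says.** All of this is in the Protocol article, Step 6: Evaluation of the Program.

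- **Candidates:** "Participant characteristics (ie, socioeconomic status [SES], age, sex, health status, and reaching health norms) will be compared at baseline".
- **Selection rule:** "Characteristics that differ for the intervention and control groups will be added as covariates in further analyses". No criterion for *differ* is given, no covariate is fixed in advance, and no other section overrides the rule.
- **Groups:** researchers recruit patients and allocate them at random to Group 1 (intervention) or Group 2 (control). In each practice "a researcher will select 10 patients that will be allocated to the intervention group and 10 patients that will be allocated to the control group". GPs then recruit Group 3 separately.
- **Analysis:** increases in physical activity, fruit and vegetable intake and self-regulation skills from baseline are compared by repeated measures MANOVA. In addition, "multilevel analyses will be conducted to take into account the clustering of participants into general practices".

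**The concern.** A covariate earns its place by predicting the outcome or, in a non-randomised comparison, by confounding it. An observed baseline difference is a poor guide to either.

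- **Groups 1 v 2.** Differences arise by chance. The rule can drop a strong predictor that happens to be balanced and admit a weak one that is not. The final model is unknown until the data are seen, and the precision that a good predictor would bring is mostly lost.
- **Group 3.** Differences may be systematic. Failing to detect a difference does not show that it is absent, so a measured confounder can stay out of the model. The article asks whether GP involvement leads to more sustained use and healthier behaviour, so this comparison matters.

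**Working it through.** **Inputs from the article.** 15 practices x 30 = 450, which reproduces the stated total. 15 x 10 = 150 per group. There are five candidate covariates.

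**Assumptions not in the article.** Two-sided alpha 0.05; *differ* read as p<0.05; outcome SD 1; independent normal covariates; no clustering; the effects, correlations and shifts named below.

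**1. How often the rule adjusts for anything, Groups 1 v 2.** The chance that at least one of five covariates differs is 1 - 0.95^5 = 0.226, and the expected number is 5 x 0.05 = 0.25. In about 77% of trials nothing would be adjusted for.

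**2. Power, Groups 1 v 2, effect 0.25 SD, one covariate with correlation rho.** SE unadjusted = sqrt(2/150) = 0.1155. Power is approximately Phi(0.25/0.1155 - 1.96) = Phi(0.205) = 58.1%. With fixed adjustment the SE is multiplied by sqrt(1 - rho^2).

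| rho | Fixed, formula | Fixed, simulated | Rule, simulated |
|---|---|---|---|
| 0.1 | Phi(0.216) = 58.5% | 57.7% | 57.4% |
| 0.3 | Phi(0.310) = 62.2% | 63% | 59% |
| 0.6 | Phi(0.746) = 77.2% | 76% | 59% |

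Formula and simulation agree to about one point. Under the rule, power stays close to the unadjusted value.

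A second simulation (five covariates of equal strength, effect 0.3 SD, 4,000 runs) gives rule v fixed set 74.0% v 77.9% at joint R2 0.1, 75.9% v 87.4% at 0.3 and 76.6% v 95.2% at 0.5.

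**3. Type I error, Groups 1 v 2, under the rule.** One covariate: about 4.5-5.4% at correlations 0.1-0.3 and about 3.3-4.7% at 0.5-0.7, over repeated runs. Five covariates: 5.2%, 4.4% and 3.8% at joint R2 0.1, 0.3 and 0.5.

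**4. Group 3 v a researcher-recruited group, no true effect, each covariate truly shifted.** The chance of detecting a 0.1 SD shift is about Phi(0.1/0.1155 - 1.96) + Phi(-0.1/0.1155 - 1.96) = Phi(-1.09) + Phi(-2.83) = 14%. For 0.2 SD it is about Phi(1.73 - 1.96) = 41%. Most such shifts would be missed. Unadjusted bias is 5 x sqrt(R2/5) x shift; for R2 0.1 and shift 0.1 that is 5 x 0.141 x 0.1 = 0.071 SD. Simulated results (4,000 runs), bias in SD and type I error:

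| Shift | Joint R2 | No adjustment | Rule | Fixed set |
|---|---|---|---|---|
| 0.1 | 0.1 | 0.071; 9.5% | 0.044; 6.4% | -0.001; 4.9% |
| 0.2 | 0.1 | 0.140; 22.1% | 0.051; 7.1% | -0.002; 4.8% |
| 0.1 | 0.3 | 0.123; 19.1% | 0.077; 9.0% | 0.001; 4.8% |
| 0.2 | 0.3 | 0.247; 56.5% | 0.092; 12.1% | 0.001; 5.2% |

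A repeat gave 0.05-0.09 SD and 7-13% for the rule. This is the same within simulation error: sqrt(0.07 x 0.93/4000) = 0.4 points at a rate of 7%.

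**The case against.** **The outcomes are changes, so the covariates may explain little.** This largely stands. Baseline is already a repeated measure in the planned MANOVA. With equal SDs, a covariate equally related to the baseline and follow-up scores has zero correlation with the change. Nothing in the article supports correlations of 0.5-0.7 between SES, age, sex or health status and change. A reader might infer from the 0.6 row that the plan gives up some 17 points of power; the documents do not support that, and the gain in Groups 1 v 2 is probably at the low end.

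**The rule does not invalidate the randomised comparison.** This stands. A reader might infer that data-driven selection inflates the false-positive rate. Step 3 of the working shows it nominal at low correlation and slightly conservative at high correlation.

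**The p<0.05 threshold is not in the article.** This is true, and it is treated here as an assumption. The article says that it is not the research protocol and that it describes the evaluation only briefly, so the missing threshold is not itself a fault. The selection principle is stated outright, however, and any threshold based on observed difference shares the weakness.

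**Group 3 bias is not demonstrated.** This is also fair. The article identifies no imbalance, it describes the GPs' choice of patients as random, and the simulated shifts affect all five covariates at once. The rule also removes part of the bias compared with no adjustment. Random choice by a different recruiter at a later step is still not random allocation between groups, and the article calls the design quasi-experimental. What stands is that the rule *can* leave measured confounding in place, not that it will.

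**Conclusion.** The concern holds as a weakness of a stated rule. For Groups 1 v 2 the cost is a data-dependent model and some lost precision: from almost nothing at a correlation of 0.1 to about 4 points of power at 0.3, and more only under correlations that the article gives no reason to expect. Validity of that comparison is not at issue. For Group 3 the cost is possible residual confounding by variables already collected: about 0.05-0.09 SD of bias and 7-13% type I error, against about 0 and 5% with a fixed set, if shifts of 0.1-0.2 SD and a joint R2 of 0.1-0.3 apply. A fixed set would not deal with unmeasured confounding. The direction of the advice does not depend on the assumed values, because five pre-specified covariates cost very little with 150 per group; only the size does.

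**What to change.** Replace the selection sentence with: *SES, age, sex, health status and reaching health norms are included as covariates in all group comparisons, whatever their balance at baseline.* Apply this within the multilevel models already planned, which deal with practice clustering, and present the baseline comparison descriptively.

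Optionally, for Groups 1 v 2, use a model for the follow-up value adjusted for the continuous baseline outcome in place of the yes/no norm indicator. With equal variances and baseline/follow-up correlation r, baseline explains (1 - r)/2 of the variance of change: 30% at r = 0.4 and 15% at r = 0.7 (assumed values). At an effect of 0.3 SD of the change score this would raise power from 74% to 87% and 80% respectively. It is more than a wording change: it replaces the repeated measures change analysis, and the plan should say so. For Group 3, change-score and baseline-adjusted analyses can estimate different things, so that choice should be made explicitly.

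The main fix costs one sentence and no new data. Its downside is a few degrees of freedom, and the loss of participants with missing covariates unless a method for handling them is stated.

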**Figure 4 figure4:**
[figure not shown]
Design of the clustered quasi-experimental trial: A clustered quasi-experimental trial with three conditions will be used to evaluate the intervention. Group 1 is an intervention group recruited by a researcher, Group 2 is a control group recruited by a researcher, and Group 3 is an intervention group recruited by a GP.

## Discussion

Using IM increases the likelihood of developing an effective eHealth intervention and the transparency of intervention components, which makes replication possible for future researchers [24]. In the first step of the IM protocol we identified that PA levels and fruit and vegetable intake of adults were lower than recommended. In Step 2, the most important individual determinants for these low levels of PA and FV intake were determined and the objectives of the program were formulated. In Step 3, behavior change techniques were selected that are thought to affect these determinants and, hence, to achieve the stated objectives. In Step 4, the eHealth intervention MyPlan 1.0 was developed. Implementation strategies were selected in Step 5 and an implementation plan was made in Step 6.

Various eHealth interventions are based on motivational theories like the theory of planned behavior [51-53]. They most often target motivational determinants that are important during the early stages of behavior change, such as attitude and knowledge. However, interventions based upon theories of intentions are often more effective in changing intentions than in changing behavior [9,16], hence revealing the so-called intention-behavior gap. Our new eHealth program was partly based on a previous eHealth program developed by Vandelanotte et al [27] and Spittaels et al [28]. This original program was also based on the theory of planned behavior [54] and the transtheoretical model [55] and only gave feedback on motivational determinants (eg, intentions, attitudes, self-efficacy, and knowledge). The strategy of tailored feedback was further integrated to target the motivational determinants, but we also searched for new strategies such as goal setting, self-monitoring, and prompt review of goal progress to target volitional determinants.

Self-regulation has recently been considered as a preferred method to overcome the intention-behavior gap and thus to promote health behavior [19,40]. Therefore, the integration of the self-regulation skills in MyPlan 1.0 that target both motivational and volitional determinants was a particular strength of our study. Previous research showed more goal ownership in participants who set their own health goals. Participants who pursue their own health goals are also less likely to drop out of behavior change programs compared to participants who get prescribed health goals [56]. Another strength is that participants have the opportunity to choose between different target behaviors and can decide themselves what they would like to change. Choice is further incorporated into the program by letting participants select for themselves what information they want to read, which goals they want to set, and which strategies they want to use. It is expected that these features will increase goal ownership, which is known to lead to more internal motivation and empowerment, and more effective behavior change [19,21,22,25,57].

A further strength of our study is the comprehensive involvement of GPs in Step 5—implementation in general practice—of the IM protocol. To ensure the feasibility of the implementation in general practice, we involved GPs from the start of the development of the intervention. During focus group interviews, important barriers for the implementation of the intervention in general practice were reported. For example, the time burden for GPs when participating in preventive actions was of major importance. Therefore, an intervention in which the personal advice was provided by a computer program was well appreciated. MyPlan 1.0 can prompt GPs to motivate their patients to adopt a healthy lifestyle, but GPs are not expected to provide extensive preventive counseling. However, some GPs will make more of an effort than others to motivate patients. Therefore, in the evaluation study all participating GPs will be asked to motivate patients to use the intervention program to set personal and attainable health goals, rather than to prescribe health recommendations and general information. Also of importance is the creation of different choices about how and when GPs may implement the intervention. Therefore, a decision tree and a list of practical solutions to implement the intervention via tablets and flyers in general practice was generated.

In Step 6—evaluation—it will be investigated whether the direct involvement of GPs in the program matters. More specifically, we will evaluate whether GPs’ involvement leads to more sustained use of the intervention and higher levels of PA and FV intake. Also, multilevel analyses will be conducted to control for the clustering of participants into different general practices. Furthermore, it will also be important to evaluate the quality of participants’ action plans because previous research has shown that action plans of participants can be of poor quality [58].

Following the IM protocol is a complex and time-consuming enterprise [44,59]. Therefore, we suggest that future researchers search for existing study protocols that describe the development of interventions and integrate similar theories and methods that can be used as the basis for their intervention programs. In our study, existing protocols were used to translate self-regulation methods into practical applications in a computer-tailored program [25,26,41]. However, as target behaviors and contexts differ, it is important to further elaborate the different steps of the IM protocol for new interventions. Our program, for example, differs from the existing protocols in several ways. First, we used a program that made it possible to deliver tailored follow-up feedback in which changes in health behavior were mentioned and compared with health goals. This makes it possible to provide detailed tailored feedback on the behavior change process. Second, the delivery mode of our program is variable, as the program can be delivered via different channels, such as via the Internet and via tablets. The delivery via tablets made it possible to deliver MyPlan 1.0 in natural settings (ie, general practice). This leads us to the third important aspect on which our program deviates from other programs [25,26,41], namely, the possibility to integrate extra personal feedback by general practitioners. In conclusion, if MyPlan 1.0 is found to be effective, a new eHealth program for the promotion of PA and FV intake that can be applied by GPs will be available. Future research can focus on designing modules for other behaviors and on evaluating other methods and effective channels for implementation.

## Appendix

Multimedia Appendix 1 Performance objectives, their related change objectives, and their determinants for the target behaviors physical activity and fruit and vegetable intake.

## Abbreviations

CAPHRI: School for Public Health and Primary Care
FV: fruit and vegetable
FWO: Research Foundation-Flanders
GP: general practitioner
IM: intervention mapping
MANOVA: multivariate analysis of variance
PA: physical activity
SES: socioeconomic status
SMART: specific, measurable, attainable, relevant, and time-bound
SMS: short message service
